### Endpoint

The primary endpoint of the study is to evaluate the technical and clinical success of EVAR with Alto stent graft in short- (90-day), mid- (1-year), and long-term (5-year) follow-up periods. Technical success is defined as the correct graft deployment without any unintentional occlusion of the aortic visceral branches or both hypogastric arteries, with aneurysm exclusion confirmed by the intraoperative angiography, without signs of type I/III endoleak or conversion to open surgery or mortality. Clinical success includes successful deployment of the endovascular device at the intended location without death as a result of aneurysm-related treatment, type I or III endoleak, or graft infection or thrombosis, aneurysm expansion (>5 mm), aneurysm rupture, or conversion to open repair. Moreover, the presence of graft dilatation of 20% or more by diameter, graft migration, or a failure of device integrity will be evaluated.

The clinical and technical successes are defined “assisted” in case of unplanned endovascular procedures, or “secondary” if unplanned surgery is necessary [19].

The following secondary endpoints will be also addressed: (1) operative time; (2) intraoperative radiation exposure; (3) contrast medium usage; (4) AAA sac shrinkage at 12-month and 5-year follow-up; (5) any potential role of patients’ baseline characteristics, valuated on preoperative CTA, and of device configuration (number of component) in primary endpoint.

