### Data Collection and Analysis

Patient data will be captured electronically using a computer-based platform accessible to all investigators. Descriptive data summaries will be used to present and summarize the collected data. For categorical variables (eg, gender), frequency distributions and cross tabulations will be given. For numeric variables (eg, patient age), range, mean, median, and SD will be calculated. For all variables, a 95% CI for the relevant parameters of the underlying distribution will be calculated. For all time-dependent events, life tables will be calculated using the Kaplan-Meier estimate method for a period starting on the date of the procedure up to and including all follow-up visits. Stratification to risk factors will be performed and the log-rank test will be used to compare between the different outcomes; associated *P* values <.05 will be defined as significant.

All preoperative and follow-up CTAs were assessed and independently evaluated by 2 experienced vascular surgeons at core laboratory center. Disagreements will be discussed and resolved by consensus.

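### The log-rank sentence names the wrong comparison, and log-rank across risk-factor strata at P<.05 is a weak sole test for secondary endpoint 5

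*Protocol article*

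**What the plan says.** Secondary endpoint 5 (Methods, Endpoint) has two parts. One is "any potential role of patients’ baseline characteristics, valuated on preoperative CTA"; the other continues "and of device configuration (number of component) in primary endpoint". The primary endpoint covers both technical and clinical success. No list of characteristics is given, and components planned before the procedure are not distinguished from those added during it.

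The analysis text (Methods, Data Collection and Analysis) gives these tools:

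- For categorical variables, "frequency distributions and cross tabulations will be given".
- Interval estimates at the 95% level for every variable.
- On survival methods: "For all time-dependent events, life tables will be calculated using the Kaplan-Meier estimate method".
- "Stratification to risk factors will be performed", and in the same sentence "the log-rank test will be used to compare between the different outcomes", with P "values <.05 will be defined as significant".

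The log-rank test is the only hypothesis test named. The article names no regression model and no rule for multiple testing. Two passages elsewhere matter here. Study Patients says that the choice of procedure depends partly on anatomy. Recruitment counts a patient as enrolled only after the procedure has succeeded on completion angiography.

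**The concern.** Taken literally, the log-rank sentence describes a comparison that the test cannot make. It compares the event-time curves of separate groups of patients on one outcome. Different outcomes in the same patients are neither separate groups nor independent.

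Once the sentence is read as intended, the method still fits endpoint 5 poorly, for three reasons.

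1. **Component number differs in kind from the CTA measures.** The CTA measures are fixed before treatment. The number of components is settled at the procedure, in a non-randomised cohort, and is plausibly linked to anatomy. A log-rank comparison by component number does not separate the two unless anatomy is also held fixed.
2. **The factor list is open and the label is bare.** Any factor that falls below .05 is called significant, however many were examined.
3. **Technical success is an intraoperative yes/no result.** It has no event time, so a log-rank test cannot address that half of the primary endpoint.

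At stake is how the risk-factor results will be read. A component-number association could be anatomy under another name, and a chance finding could be published as a predictor.

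**Working it through.** The plan gives no figure to reproduce: 300 patients is an estimate without an effect size, event rate or power. The checks below size the consequences under stated assumptions.

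**1. Chance of a false predictor.** From the article: the .05 threshold. Assumed: the number of factors k, with every factor null and independent. The anatomical criteria under Device Under Investigation give a plausible lower figure. They name seven measures (thrombus, calcification, conicity, sealing-zone diameter, aortic angle, iliac landing length, iliac diameter), and component number makes eight.

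Formula: 1 − 0.95^k.

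| k | Chance of at least one false positive | Expected number (0.05 × k) |
|---|---|---|
| 8 | 1 − 0.95^8 = 33.7% | 0.4 |
| 10 | 1 − 0.95^10 = 40.1% | 0.5 |
| 20 | 1 − 0.95^20 = 64.2% | 1.0 |

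Anatomical factors are likely to be correlated, and positive correlation would lower the middle column. The expected number does not depend on independence.

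**2. Information available.** From the article: 300 patients and 5 years of follow-up. Assumed: 5%, 10% or 20% clinical failure by 5 years, so 300 × 0.05 = 15, 300 × 0.10 = 30 or 300 × 0.20 = 60 events. Log-rank power (Schoenfeld, two-sided .05) for a hazard ratio (HR) of 2 with a 50:50 factor:

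| Events | Power |
|---|---|
| 15 | 26.8% |
| 30 | 47.5% |
| 60 | 76.6% |

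Events needed for 80% power at HR 2 are (1.96 + 0.842)² / [p(1 − p)(ln 2)²]. This gives 66 for a 50:50 factor and 88 for a 25:75 factor. At about one parameter per 10 events, 30 events support about 3 parameters and 60 support about 6. Real predictors may therefore be missed, while false ones still appear at the rates in step 1.

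**3. Component number and anatomy.** Simulation with 1,000 runs per scenario, 300 patients, 5 years, about 10% failures and no true effect of component number. Assumed: 30% of patients have hostile anatomy. The other inputs, also assumed, are in the table. The last two columns show how often component number is declared significant at .05.

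| Extra components: hostile / other | Failure HR, hostile anatomy | Log-rank, unadjusted | Log-rank stratified by anatomy |
|---|---|---|---|
| 30% / 30% (no link) | 3 | 4.2% | 4.6% |
| 40% / 20% | 2 | 6.6% | 4.1% |
| 50% / 15% | 2 | 11.5% | 3.8% |
| 50% / 15% | 3 | 22.1% | 4.9% |
| 60% / 10% | 3 | 38.5% | 4.5% |

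If component number and anatomy are linked, the unadjusted test is wrong in 7% to 39% of runs. Holding anatomy fixed restores about 4% to 5%. If they are not linked, there is no inflation. The documents do not say which case applies.

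**4. Technical success.** Endpoint defines it from the intraoperative angiogram, without a type I or III endoleak, conversion or death. Recruitment admits patients only after a successful procedure on completion angiography. Failures among enrolled patients will therefore be close to absent by design, and a binary regression would have almost nothing to model.

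**The case against.** The strongest reply is that the wrong word is a slip. The sentence opens with stratification to risk factors, so groups were evidently meant, and changing the word changes no result. That stands, and the wording alone would be a minor correction.

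The reply goes further, and several stronger readings do fail.

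- A reader might infer that each factor will be tested alone, unadjusted and with forced cut-points. The article says none of this. Stratification with a log-rank test is compatible with a stratified log-rank, which does adjust; step 3 shows that stratifying on anatomy would work.
- A reader might call the absence of a multivariable model or multiplicity rule an error. This is a condensed article. A full protocol or analysis plan may contain both, so their absence is not the finding.
- A reader might infer that extra components are placed because a seal was not achieved, making component number partly a consequence of failure. That is reasonable, but the documents do not state it. They relabel success after unplanned procedures without linking this to component count.
- A reader might infer that log-rank is assigned to technical success. It follows the Kaplan-Meier sentence on time-dependent events, and cross tabulations and confidence intervals remain available for a binary result.

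It is also fair that this is the fifth secondary endpoint, phrased as a search for any potential role, in a registry that describes itself as descriptive.

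What the reply does not remove is the method on the page. The one inferential procedure named for this endpoint is log-rank across risk-factor strata, with results below .05 called significant. Cross tabulations and confidence intervals carry no adjustment either.

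**Conclusion.** The point holds in limited form. The log-rank sentence misstates what is compared. The stated method for secondary endpoint 5, used as written, can report confounded or chance associations as significant predictors.

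The chance of at least one false positive is 34% to 40% with 8 to 10 independent null factors, and 64% with 20. The factor counts and independence are assumptions. The size of any confounding of component number by anatomy cannot be fixed from the documents; the 7% to 39% range rests wholly on assumed inputs. The link itself is plausible rather than stated.

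The effect is confined to the reading of the risk-factor results. Nothing here supports a claim that the primary endpoint estimates are affected, or that patient selection would be changed; the article ties selection to the instructions for use. The change is worth making because it is cheap and because planned component number becomes harder to recover with time.

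**What to change.** 1. **Reword the sentence**, for example: *Kaplan-Meier curves for time to clinical failure will be shown by prespecified risk-factor group, and groups of patients will be compared with the log-rank test.*
2. **For endpoint 5, use one Cox model for clinical failure.** Enter a short prespecified set of CTA measures, kept continuous, together with component number. Limit the number of parameters by the events observed, and penalise the model if events are few. Report hazard ratios with 95% CIs as exploratory, without the significance label.
3. **Use the component number planned at sizing** rather than the number finally implanted, where the record allows.
4. **Report technical success descriptively as a binary result** and do not model it, given the enrolment rule.

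If the full protocol or analysis plan already contains such a model, the article text need only be aligned with it.

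The cost is analysis wording, some modelling work and fewer headline P values. Item 3 may need retrospective retrieval for patients already enrolled, since enrolment began in January 2022. No change to sample size, visits or imaging is needed.

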### Recruitment

An estimated number of 300 patients submitted to EVAR with Alto stent graft will be enrolled. It is estimated that the inclusion period will be 24 months. The follow-up period is set to be 5 years. Prior to enrollment into the clinical investigation, patients will be evaluated by their physician for inclusion criteria. Each patient’s medical condition should be stable, with no underlying medical condition that would prevent them from performing the required testing or from completing the study. Patients should be geographically stable, willing and able to cooperate in this clinical study, and remain available for midterm follow-up. Patients who do not wish to participate in this study can obtain the best available EVAR therapy as indicated; refusal to participate in this study will in no way affect their care at the institution. Inclusion and exclusion criteria are detailed in Textbox 1.

This study respects all the principles reported in the current version of Helsinki declaration (2013). AAA morphology will be assessed by OsiriX MD (OsiriX software; PIXMEO) on a computer (with Mac operating system) in a preoperative, contrast-enhanced, computed tomography angiographic (CTA) study. CTA must be performed with a biphasic acquisition protocol (unenhanced and contrast-enhanced scanning with a bolus tracking system) and reconstructions to 1-mm slices. All measurements (diameter, length, and angles) will be evaluated on a workstation with dedicated reconstruction software and center lumen line analysis and multiplanar reconstruction.

Inclusion and exclusion criteria.

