## Results

Patient enrollment started in January 2022. It is anticipated that 300 patients will be recruited to the study. All variables will be evaluated in a dedicated central database. All morphological changes will be examined in a centralized core laboratory. After data analysis, results will be shared with each investigator. Updates to results will be published at 1-year follow-up and at 3-5-year follow-up.

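### An unadjusted P<.05 is defined as significant for an open-ended search for risk factors, so the chance of at least one false predictor is well above 5%

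*Protocol article*

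**What the plan says.** Three parts of the protocol article bear on this point.

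- **Data Collection and Analysis** sets the method: "Stratification to risk factors will be performed and the log-rank test will be used to compare between the different outcomes". The same sentence gives the decision rule, that associated P "values <.05 will be defined as significant". It names no factors, gives no number of tests and does not mark the comparisons as exploratory.
- **Endpoint** supplies what is to be tested. Under the words "The following secondary endpoints will be also addressed", item 5 is "any potential role of patients’ baseline characteristics, valuated on preoperative CTA, and of device configuration (number of component) in primary endpoint". Number of components is the only factor singled out; the CTA characteristics are left open. The primary endpoint itself covers technical and clinical success over "short- (90-day), mid- (1-year), and long-term (5-year) follow-up periods".
- **Results** says when findings appear: "Updates to results will be published at 1-year follow-up and at 3-5-year follow-up". It does not say which analyses each update contains.

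Under Ethical Consideration, the registry is presented to review boards as descriptive and nonexperimental.

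**The concern.** A threshold of .05 limits the false-positive chance of one test. Secondary endpoint 5 is a search over an unstated number of tests, and the rule attaches the word significant to any of them that passes. With no true predictor at all, the chance that the search yields at least one declared predictor grows with the number of factors examined.

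The stake is how the results will be read. The Discussion gives the registry's purpose as showing safety and effectiveness across different anatomical scenarios, and the Conclusions link the redesign to a wider range of on-label anatomies. A neck or access feature published as a significant predictor of failure would bear directly on that message, even if it came from one of several unadjusted tests. The significance rule is also the one inferential declaration in an otherwise descriptive analysis section, and it falls on the analysis whose content is least fixed in advance.

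**Working it through.** **No figure to reproduce.** The article states no family-wise error rate, power or event rate. The sample size comes without a derivation: "An estimated number of 300 patients submitted to EVAR with Alto stent graft will be enrolled". The only stated figure is the per-test threshold of .05.

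**Inputs**

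- Per-test level: .05 (Data Collection and Analysis). Sidedness is not stated; two-sided is assumed, so the critical value is c = 1.96.
- Number of factors, k: not stated. **Assumption:** 5 to 9. The upper value counts the anatomical items listed under Device Under Investigation (access, thrombus, calcification, conicity, neck diameter, aortic angle, iliac length, iliac diameter: eight) plus number of components.
- Correlation between test statistics, ρ: not stated. **Assumption:** 0 to 0.8, equal for all pairs.
- Each factor is tested once, on one outcome, and none has a true effect.

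**Independent tests (ρ = 0).** The chance of at least one P<.05 is 1 − 0.95^k.

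- k = 5: 1 − 0.95^5 = 0.226
- k = 9: 1 − 0.95^9 = 0.370

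**Correlated tests.** With equicorrelated standard normal statistics, the chance is

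1 − ∫ φ(u) [Φ((c − √ρ·u)/√(1−ρ)) − Φ((−c − √ρ·u)/√(1−ρ))]^k du.

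| k | ρ = 0 | ρ = 0.5 | ρ = 0.8 |
|---|---|---|---|
| 5 | 22.6% | 18.3% | 12.7% |
| 9 | 37.0% | 26.9% | 16.6% |

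Numerical integration and simulation agree to rounding. Divided by 5%, the range runs from 12.7/5 = 2.5 to 37.0/5 = 7.4.

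**Does a false declaration become more likely than not?** Not at these counts. With independent tests, 1 − 0.95^k first exceeds one half at k = 14 (1 − 0.95^14 = 0.512; k = 13 gives 0.487). With correlated tests it needs more factors: at ρ = 0.5, even k = 20 gives 42%.

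**If tests were rerun at a later update (conditional).** For a single null factor tested at assumed information fractions 0.4 and 1.0, the chance of at least one P<.05 is about 9%. For nine factors at 0.3 and 1.0 it is about 43% (ρ = 0.5) to 57% (ρ = 0). These figures show direction only, because neither the rerun nor the information fractions are in the article.

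**The case against.** **Left to a fuller document.** A journal article may leave the factor list and the handling of multiplicity to a full protocol or SAP, and those omissions are not counted here. What stands against the article is the rule it does state. A later plan that adjusted, or withheld the word significant, would depart from the published rule; one that did not would inherit it.

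**.05 is a per-test convention.** This is correct. The article claims no family-wise rate, so no stated figure is contradicted. The multiples above show what the rule does when applied to a search; they do not show that a promise was broken.

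**The factor count is weakly sourced.** This also stands. The nine items come from instructions-for-use criteria, and the inclusion and exclusion criteria admit only patients treated within those instructions. Every enrolled patient meets conditions such as adequate access and absence of significant thrombus or calcification, so stratifying on those conditions as written gives no comparison group. Finer gradations could be examined, but the article does not say so. Nine is therefore one value in an assumed range.

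**Stronger readings.** A reader might infer that the tests are repeated at each published update. The Results section promises updates without saying that the log-rank tests are rerun, so this is permitted but not stated. A reader might also infer that a false predictor is likely to be announced. The single-analysis figures of 13% to 37% do not support that.

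**Limited weight.** The search is the fifth secondary endpoint of a descriptive registry, is worded tentatively, and carries no power claim. The section already plans 95% CIs. No passage ties a risk-factor P value to a decision on device use. This limits the seriousness of the point, but the descriptive character also argues for an exploratory label.

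**Conclusion.** The point holds as a cheap improvement. The article fixes an unadjusted P<.05 as its definition of a significant risk factor and applies it to a search of unstated size. On the assumption of five to nine null factors each tested once, the chance of at least one false declaration is about 13–23% (five) to 17–37% (nine) for correlations of 0.8 to 0, which is several times the 5% per-test level. The direction does not depend on the exact count, since any search over more than one factor exceeds 5% unless the tests are fully redundant. The size depends on k and ρ, neither of which the article gives. The calculation uses one outcome and one analysis; more outcomes or repeat testing would raise it. The descriptive estimates of technical and clinical success are untouched.

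**What to change.** In Data Collection and Analysis, replace the significance rule for secondary endpoint 5 with wording such as:

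> Risk-factor comparisons are exploratory; they are reported as effect estimates with 95% CI together with the number of factors examined, and no factor is declared significant from an unadjusted P value.

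Only if a formal claim is wanted, restrict it to a listed set of factors tested once, at the 5-year analysis, with a multiplicity adjustment such as Holm. With nine factors the first Holm step would be .05/9 = .0056. In a registry's secondary endpoint this is optional, because it trades sensitivity for error control.

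**Cost:** one or two sentences of analysis wording, with no extra patients, visits or data. The downside is that fewer factors can be called significant, and associations in the earlier publication would be presented as exploratory.

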### Patients’ Confidentiality

All information and data concerning patients or their participation in this clinical investigation will be considered confidential. Only authorized personnel will have access to these confidential files. Authorized personnel of health authorities will have the right to inspect and copy all records pertinent to this clinical investigation. All data used in the analysis and reporting of this clinical investigation will be anonymized.

### Ethical Consideration

This study adheres to the guidelines of European Good Clinical Practice (ICH: 6 R2) and adopted by the Italian Agenzia Italiana del Farmaco (AIFA), in accordance to Legislative Decree 196/2003 and 21/2007 of the Italian Ministry of Health. The local institutional review boards of the participating centers were informed of the descriptive, nonexperimental nature of this registry study. The device under investigation is already available for standard clinical practice.

### Data Availability

The data sets generated during or analyzed during this study will be available from the corresponding author on reasonable request.

## Results

Patient enrollment started in January 2022. It is anticipated that 300 patients will be recruited to the study. All variables will be evaluated in a dedicated central database. All morphological changes will be examined in a centralized core laboratory. After data analysis, results will be shared with each investigator. Updates to results will be published at 1-year follow-up and at 3-5-year follow-up.

## Discussion

The purpose of this registry study is to demonstrate that the adaptive sealing technology of the Alto stent graft is safe and effective in the treatment of infrarenal AAA in different anatomical scenarios.

Since its appearance in the market in 2010, the Ovation endograft has offered an innovative sealing concept involving a nonexpansive circumferential apposition of inflatable rings filled by a low-viscosity polymer [20]. The polymer-filled system adapts to the patients’ aortic neck, thus ensuring a continuous, customized concentric seal. This feature allows a broadening of patient’s eligibility that is higher than other stent graft [21].

The Ovation Alto abdominal stent-graft system received Food and Drug Administration (FDA) approval on March 16, 2020. The commercial launch of the device in the United States was announced on July 30, 2020. On August 5, 2020, Endologix proclaimed CE Mark approval in the European Union for EVAR. In Italy, the commercial launch started in November 2020, in centers having a vast experience with Ovation Prime and iX. The new Alto sealing zone is closer to the renal arteries and may offer sealing in aneurysms with irregular or less than 1-cm long neck. We have already described the possibility to treat juxtarenal aortic aneurysms unfit for open surgery and for fenestrated/branched EVAR. The solution was to perform a physician-modified implantation of Ovation iX, in a procedure termed the “vent” technique. It involves an off-label, aggressive deployment of the sealing ring between 1 and 3 mm below the lowermost renal artery rather than 13 mm. The proximal edge of the collar zone’s fabric was moved down by bare-metal stents contemporarily deployed to assure renal arteries’ patency [22]. The vent technique offered a preliminary evaluation of how the polymer ring may behave close to the renal ostium in very challenging necks, which is now possible with the new design of the Ovation Alto.

An inaccurate deployment of the sealing ring with the previous Ovation version has been described as the cause for an early technical failure [23]. The compliant balloon in the new version of the Alto stent graft may help operators to identify the first ring’s landing, thereby making the deployment more precise. Moreover, the sealing ring’s early ballooning may guarantee a more accurate customization of polymer to aortic wall shape.

The low-profile delivery system (15 F) establishes small iliac access (>6 mm) with the possibility to perform percutaneous procedures, achieving a reduction in blood loss, groin complications, and earlier discharge.

Holden and Lyden [24] reported promising results in the first-in-human experience with the Ovation Alto. At the moment, only early outcomes in a series of 7 patients have been published, while the 5-year results from the Expanding Patient Applicability with Polymer Sealing Ovation Alto Stent Graft (ELEVATE) clinical trial are expected to be published in 2023.

Recently, another initial experience [25] confirmed the early technical and clinical success of the new Ovation Alto stent graft.

Good 5-year EVAR results with the Ovation platform have been reported, demonstrating excellent long-term durability of this endograft, despite 41% of patients having an anatomy unfit for other stent grafts [26]. Results from our registry study may further confirm durability results with the novel version. Moreover, the technical modifications to the endograft may allow for accommodation of a more comprehensive range of anatomies on-label.

